## **5. Methods:**

### **5.1. Subject criteria**

One hundred forty pregnant women who are healthy and have no history of MDE will be recruited during their third trimester and such that at least 100 completing subjects will be enrolled to complete the study. Participants will be recruited by advertisement (see end of section 5.1 for further detail regarding advertising). Subjects expressing interest at earlier times in pregnancy will have their initial visit booked in the third trimester (i.e. in person completion of screening questionnaires to rule out a psychiatric disorder and final verification of other requirements). Subjects will randomly be assigned to placebo or active supplement in a double blind manner within blocks of 2, 4, 6, 8 or 10 subjects. Block size will be randomly selected using standard randomizing software. The supplements/placebo will be taken at 4 time points, starting on day 3 postpartum night to day 5 postpartum morning (See table 2 for full schedule). Subjects will receive either the dietary supplement or a placebo that matches in taste and colour (as verified by independent manufacturer and investigator for visual and taste testing during placebo product development) (this has already been created). On day 5 postpartum, participants will be seen for a single visit (at their house).

### **Inclusion Criteria:**

- I. The subject, as reported by them, should be in good health.
- II. The subject is not taking any medication, with the exception of medications used to manage illnesses or conditions not implicated in affecting mood state.
- III. The subject is not taking any investigational medicinal product within 8 weeks.
- IV. Age 18 to 45
- V. BMI 18.5 to 40 ( $\text{kg/m}^2$ ) (based on participant self-report of pre-pregnancy weight and height)
- VI. Resting pulse between 45 and 100 bpm
- VII. Systolic blood pressure between 91 and 139 mmHg (inclusive)
- VIII. Diastolic blood pressure between 51 and 90 mmHg (inclusive)
- IX. Orthostatic blood pressure change  $<20$  mmHg (based on the difference between supine and standing (1 minute) systolic blood pressure)

## **A Dietary Supplement for Mood Symptoms in Early Postpartum: A Double Blind Randomized Placebo Controlled Trial**

### **Exclusion Criteria:**

- I. The subject has been diagnosed with any disorders based on Structured Clinical Interview (SCID) for DSM-5 interview  within the past 10 years.
- II. Subjects who have been smoking cigarettes in the past 5 years (to reduce variability in mood attributable to cigarette withdrawal and MAO-A).
- III. Current substance abuse
- IV. Known intolerance to specific components of tryptophan, tyrosine and blueberry
- V. Currently taking MAO inhibitors and serotonergic drugs (including serotonin reuptake inhibitors; serotonin and norepinephrine reuptake inhibitors; tricyclic antidepressants; triptans; lithium; dextromethorphan; opiate medications with off target serotonergic effects such as methadone, pethidine (meperidine), tramadol, fentanyl, tapentadol; and serotonin agonists), as well as antiparkinsonian drugs. Ondansetron, an anti-nausea agent which is a blocker of serotonin at the 5-HT3 receptor and opposes effects of serotonin is not included as exclusionary
- VI. Currently taking morphine which would affect mood
- VII. Any medical illness that would affect mood state as assessed by the principal investigator  
Exclusionary Medical Illnesses include:
  - 1) Endocrine diseases requiring ongoing medication including hypo or hyperthyroidism
  - 2) Frequent migraines (greater than one per week on average)
  - 3) Neurological illnesses with the exception of infrequent migraines, and benign essential tremor
  - 4) Neoplasm that is not benign
  - 5) Pre-eclampsia/eclampsia
  - 6) Autoimmune diseases without full recovery for more than 5 years
  - 7) Metabolic diseases

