### **Withdrawal criteria:**

Participants who have been enrolled into the study as per the eligibility criteria listed above would be withdrawn from the study, should they meet any of the following criteria:

- I. If in the principal investigator's judgement the obstetric or neonatal complications were so severe that would cause change in the results of the study, such as infant death, the subject will be withdrawn from the study (the purpose is to avoid undue burden on participants and to avoid biased results of mood induction).
- II. Evidence of substance abuse based on the urine test results done on day-5 postpartum (the results of the urine test would be available 1-2 weeks later but removal of mood induction data biased by substance abuse would improve data integrity).
- III. If the participant shows any allergic reaction or significant side effects to any components of the dietary supplement that would make continued participation harmful.
- IV. Participant is recommended or required by their health care practitioner to take methadone, pethidine (meperidine), tramadol, fentanyl tapentadol, or morphine within 12 hours prior to taking their tryptophan dose scheduled on day 4 postpartum.
- V. If in the principal investigator's judgment continuing the study is no longer in the participant's best interest.

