## **5.2. Dietary Supplements**

**The active dietary supplement consists of:** 2 grams of tryptophan, 10 grams of tyrosine, blueberry juice and blueberry extract (with different schedules of administration for each). The tryptophan will be 1 g tablets (exactly what has been tested in our previous studies). Tryptophan will be obtained as L-tryptophan tablets from Apotex. Each container contains 100 of 1 gram tryptophan tablets. Tyrosine will be obtained as L-Tyrosine capsules from Natural Factors. Each container has 90 capsules of 500 milligram L-tyrosine capsules. The blueberry extract powder is called VitaBlue and will be purchased from Future-Ceuticals. The active blueberry pouches contain 2.02 grams of VitaBlue (product N1077) and 11.54 grams of sugar from Caldic. These pouches will be packaged by NSF-GFTC. The blueberry juice consists of 35.5 grams of blueberry juice concentrate from ProIngredients MILNE, 2.66 grams of blueberry flavor from Bell Flavors, 21.3 grams sugar and 0.36 grams of citric acid from Caldic and 282.63 grams of water. The blueberry juice is packaged in glass containers by NSF-GFTC. With the exception of the tryptophan and tyrosine, the amounts listed for each item listed in the active dietary supplement and placebo (see below for placebo), are approximate, being within 5% of the listed amounts.

**The placebo consists of:** The placebo pills appear identical to tryptophan and tyrosine pills and will be prepared by CAMH pharmacy. Empty hard gelatin capsules from Capsugel and Lactose monohydrate from Galenova for placebos to match tryptophan and tyrosine. Tryptophan pills will also be over encapsulated to match the placebos. The placebo pouches (to match the blueberry extract) contain 1.02 grams of Shade grape blue powder from GNT and 12.54 grams of sugar from Caldic. The placebo drink is a natural drink that is blue through natural colouring, has a flavour like blueberry through natural flavoring, and has negligible antioxidant properties and similar sugar levels to the active drink. The placebo blueberry beverage consists of 3.55 grams of blueberry flavor from Bell Flavors, 21.30 grams of sugar and 0.71 grams of citric acid from Caldic, 0.89 grams of Shade Bordeaux from GNT and 316 grams of water. The placebo pouches and placebo beverages are package by NSF-GFTC.

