**Timing of administration of study products:**

- Night of day 3 postpartum: Participants will mix one pouch of active or placebo extract with one active or placebo juice and drink at once
- Morning of day 4 postpartum: Participants will mix one pouch of active or placebo extract with one active or placebo juice and drink at once
- Night of day 4 postpartum: Participants will mix one pouch of active or placebo extract with one active or placebo juice and take the 2 grams of tryptophan (2 capsules of 1 gram tryptophan each) or placebo with the beverage
- Morning of day 5 postpartum (main study day): Participants will mix one pouch of active or placebo extract with one active or placebo juice and take the 10 grams of tyrosine (20 capsules of 500 milligrams tyrosine each) or placebo with the beverage

**Blinding:** The ratio of active treatment to placebo will be 1:1. Since the supplement appears likely to prevent postpartum blues on an individual case level, additional care is being taken in regards to the randomization process. The assignment of placebo supplement or active supplement will be done by the research pharmacy department who randomizes subjects evenly to each condition within blocks of 2, 4, 6, 8 or 10 subjects. Each block size will be randomly selected using standard randomizing computer software. Then, for each block subjects will be randomly selected to either protocol. For example, if a block is of size 8, four ordered numbers will be randomly assigned to one group and the remaining 4 numbers will be assigned to the other group. Each subject will be recorded in relation to a code number. The administration of the mood induction procedure and the supplement will be done on day 5 postpartum by an expert who is blinded to both.

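### The intolerance exclusion names only the active ingredients, although the placebo capsules are filled with lactose and 20 of them are taken shortly before the mood test

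*Protocol*

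**What the plan says.** - **Eligibility.** Section 5.1, Exclusion IV, lists "Known intolerance to specific components of tryptophan, tyrosine and blueberry". No inclusion or exclusion criterion mentions lactose or any other placebo ingredient.
- **Placebo composition.** Section 5.2 makes the placebo pills from "Empty hard gelatin capsules from Capsugel and Lactose monohydrate from Galenova for placebos to match tryptophan and tyrosine". The amount of lactose per capsule is not given. The active tryptophan is also over-encapsulated so that it looks the same, but no filler is stated for it.
- **Number of capsules.** Under the timing of administration in section 5.2, two capsules (tryptophan or placebo) are taken on the night of Day 4. On the morning of Day 5 the participant takes "10 grams of tyrosine (20 capsules of 500 milligrams tyrosine each) or placebo with the beverage".
- **Order on Day 5.** Table 2 puts the last dose at the start of the visit, then the first neutral induction with its VAS, then the sad induction with its VAS. Section 5.5 bases the primary analysis on depressed-mood VAS before and after the sad induction.
- **Withdrawal.** Criterion III concerns "any allergic reaction or significant side effects to any components of the dietary supplement that would make continued participation harmful". Criterion V is general: "If in the principal investigator's judgment continuing the study is no longer in the participant's best interest".

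**The concern.** The protocol recognises that known intolerance to what a woman will swallow is a reason not to enrol her, but it applies that rule to only one of the two products. The placebo is not inert for someone who is lactose intolerant, and the largest number of capsules falls on the morning of the primary assessment.

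Two things are at stake. The first is participant welfare: a woman five days postpartum could be given something she already knows disagrees with her. The second is the neutrality of the comparator. The trial exists to separate the supplement's effect from placebo response, so the placebo should not carry an avoidable effect of its own close to the outcome measurement.

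**Working it through.** This is mainly a reading of the text, with simple arithmetic on clock times. The protocol states no figure on this point to reproduce.

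**1. Is a woman with known lactose intolerance eligible?** Exclusion IV names tryptophan, tyrosine and blueberry. Lactose is in none of these; it appears only in the placebo description in section 5.2. The other places that might catch her do not do so by their terms:
- Inclusion I asks for self-reported good health.
- Exclusion VII concerns illnesses that would affect mood. Its list includes an undefined entry for metabolic diseases, but does not name food intolerance.
- Visit 1 (section 5.4.3) includes a standardized health questionnaire, but no criterion says what to do if lactose intolerance is reported.

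She is eligible as written.

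**2. Chance of exposure.** Allocation is 1:1 (section 5.2, Blinding), so the chance of receiving placebo is 1/2 = 50%.

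**3. Timing relative to the endpoint (Table 2).**
- Visit start 8:30 ± 15 min; first neutral induction 9:30 ± 30 min; sad induction 10:20 ± 30 min.
- Visit start to sad induction: 10:20 − 8:30 = 110 min. Across the windows: 9:50 − 8:45 = 65 min to 10:50 − 8:15 = 155 min.
- Visit start to first neutral induction: 9:30 − 8:30 = 60 min. Across the windows: 9:00 − 8:45 = 15 min to 10:00 − 8:15 = 105 min.
- The dose follows arrival and the medication review, so the interval from dose to sad induction is somewhat shorter than 110 min on the nominal schedule.

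**4. What this does to the primary endpoint.** Both the before and the after VAS ratings come after the dose. Write the gut-related addition to a woman's VAS as *b* at the before rating and *a* at the after rating. Her change score is altered by *a* − *b*.
- Symptoms already present and steady: *a* = *b*, so the contribution is 0.
- Symptoms that start or worsen between the ratings: *a* > *b*, so the shift is enlarged.
- Nominally the two inductions start 10:20 − 9:30 = 50 min apart, and each lasts about 15 to 20 min. If the first VAS after each induction is used, symptoms must change within roughly that 50-minute interval to matter.

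**5. Lactose load, as an illustration only.** *Assumption:* 0.3 to 0.7 g lactose per tyrosine-matched capsule (0.5 g if it equals the 500 mg replaced) and 0.5 to 1.0 g per tryptophan-matched capsule.
- Day 5 morning: 20 × 0.3 = 6 g to 20 × 0.7 = 14 g (20 × 0.5 = 10 g).
- Day 4 night: 2 × 0.5 = 1 g to 2 × 1.0 = 2 g.

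The protocol gives no dose at which symptoms are expected and no share of women with intolerance, so these loads cannot be converted into a VAS effect.

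**6. Withdrawal III against the rest.** Section 5.1 sets the two products apart: "Subjects will receive either the dietary supplement or a placebo that matches in taste and colour". Read that way, III covers the active product only. Sections 5.4.4 and 5.4.6 and the Compliance paragraph, however, use the same term for what every participant receives, placebo included. The scope of III is therefore unclear.

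**The case against.** The strongest case against is that the gap is one of wording, and that several inferences a reader might draw from it go further than the protocol allows.

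- **That the withdrawal rules also protect only the active arm.** Not supported. Criterion V applies to any participant. Criterion III uses a term that the protocol often applies to both arms, and blinded staff could not restrict it to active-arm women in any case. This stands. But V acts only once a problem has arisen and does not change who is eligible.
- **That the placebo will make her unwell.** Not shown. Fill weight, symptom threshold and prevalence are all absent. The text supports only that it may.
- **That the bias can be sized.** One could assume that 5–20% of placebo women are affected and that their shift rises by 10–20 mm. That gives 0.05 × 10 = 0.5 mm to 0.20 × 20 = 4 mm, or about 4–36% of the 11.25 mm effect in section 5.6 (25% of 45 mm) and about 2–18% of the 22.5 mm effect. Every input is assumed, and the calculation ignores the cancellation shown above. It should not be quoted as an estimate.
- **That everything pushes towards the supplement.** Only the change-score route has that sign. A blinded woman with gut symptoms could equally take them as a sign of the active product, so the effect on guessing allocation has no settled direction.
- **That the problem is confined to placebo.** Not established, because any filler in the over-encapsulated tryptophan and the excipients of the commercial products are not stated.

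It is also fair to say that consent is discussed before enrolment and that the consent form is not in the text at hand, so women may be told about the lactose. That would soften the point but would not make known intolerance an exclusion.

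**Conclusion.** The point holds as a gap in one eligibility criterion. Exclusion IV does not cover placebo components, the placebo capsules contain lactose, and nothing else in the protocol closes the gap. A woman with known lactose intolerance can be enrolled and has an even chance of taking 20 lactose-filled capsules nominally up to about 110 minutes before the sad induction.

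For the primary comparison the consequence is possible rather than demonstrated. It requires symptoms that begin or worsen between the two VAS ratings, and its size cannot be derived from the protocol. The case for acting rests on participant safety and a neutral comparator, together with the low cost of the change, not on a calculated bias. The scope of Withdrawal III is a separate, smaller inconsistency of terms.

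**What to change.** Extend Exclusion IV to known intolerance or allergy to any component of either study product as supplied, active or placebo, with lactose named, and add one matching question at screening. The cost is that question and the loss of a few otherwise eligible women. It reaches only women who know of their intolerance.

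Reconcile Withdrawal III with sections 5.1 and 5.2 so that it is clear whether placebo components fall within it; this review proposes no wording for that rule. State the lactose content per placebo capsule and any filler in the over-encapsulated tryptophan, so that the exposure in each arm can be judged.

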### **Withdrawal criteria:**

Participants who have been enrolled into the study as per the eligibility criteria listed above would be withdrawn from the study, should they meet any of the following criteria:

- I. If in the principal investigator's judgement the obstetric or neonatal complications were so severe that would cause change in the results of the study, such as infant death, the subject will be withdrawn from the study (the purpose is to avoid undue burden on participants and to avoid biased results of mood induction).
- II. Evidence of substance abuse based on the urine test results done on day-5 postpartum (the results of the urine test would be available 1-2 weeks later but removal of mood induction data biased by substance abuse would improve data integrity).
- III. If the participant shows any allergic reaction or significant side effects to any components of the dietary supplement that would make continued participation harmful.
- IV. Participant is recommended or required by their health care practitioner to take methadone, pethidine (meperidine), tramadol, fentanyl tapentadol, or morphine within 12 hours prior to taking their tryptophan dose scheduled on day 4 postpartum.
- V. If in the principal investigator's judgment continuing the study is no longer in the participant's best interest.

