### ***Methods:***

One hundred forty pregnant women who are healthy and have no history of MDE will be recruited, typically during their third trimester and it is expected 100 subjects to complete the study. They will be randomized in a double blind manner within blocks of 2, 4, 6, 8 or 10 subjects. Women will start taking the dietary supplement at 4 time points (as indicated in table 2) from day 3 postpartum to day 5 postpartum.

Using a supplement with the same ingredients as a recent open trial, the supplement consists of 2 grams tryptophan, 10 grams tyrosine and blueberry juice/extract. The only difference is that we propose to give a similarly equivalent but non-identical blueberry juice and extract. The volume of the blueberry extract is 2 grams. The appearance and taste of the placebo is indistinguishable from active treatment (as verified by independent manufacturer and investigator visual and taste testing during placebo product development).

Sad mood induction will be done based on the Velten Mood Induction Procedure (MIP). followed by presented with a piece of sad music, from work by Clark et al . Clinical rating measures of mood and symptoms of depression will be assessed before and after MIP.

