### **5.4.4. Procedures after First Visit and Before Giving Birth**

- Enrollment confirmed based on participant's full eligibility once urine test results have been obtained and assessed.
- Subjects will be randomized by CAMH pharmacy in a double-blind manner for receiving the dietary supplements (i.e. the rater and the subject will be blinded) (See section 5.2).
- Subjects will receive the package containing dietary supplement package for doses to be taken on day 3 postpartum night, day 4 postpartum morning, day 4 postpartum night and day 5 postpartum morning up to two months prior to their estimated due date. There will be a phone call to arrange a delivery time for the supplement and to provide instructions regarding its use.
- Participants will be contacted between 2 to 8 times, at a frequency of every several days to weeks based on their preference, and estimated time until due date in order to gain update about their delivery status. We will suggest 2 to 3 times as being a reasonable number and then accommodate participant preference.

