### **5.4.6. Procedures from Day 3 to Day 5 Postpartum**

- Subjects will start taking the dietary supplement from day 3 postpartum (as shown in Table 2 section 5.4). They will be ingesting a total of 4 drinks over the course of 3 days, which 3 of them will be taken over 2 days prior to the second visit (two drinks are mixture of blueberry juice and blueberry extract, and one will be 2 g tryptophan in the form of tablets taken with the mixture of blueberry juice and blueberry extract) and the fourth drink mixture will be taken on the second visit which will be 10 g tyrosine in the form of capsules taken with the mixture of blueberry juice and blueberry extract.
- Each participant is contacted 3 times to be reminded for dietary supplement intake.
  - On day 3 postpartum night prior to the intake of the first dose, they will receive a call between 6 to 9 pm. At least 3 tries should be made if unavailable at first call. The calls will be documented in contact log. Safety and tolerability checklist and concomitant medications review will also be completed on day 3 postpartum. During this phone call, the participant will also be asked about any symptoms of COVID-19. If a participant has been screened as positive (answered "yes" to any of the questions), she will be withdrawn from the study.
  - This procedure will be repeated on day 4 postpartum morning between 8 am to 10 am and prior to the intake of the second dose and,
  - One on day 4 postpartum night between 6 pm to 9 pm prior to the intake of the third dose. The safety and tolerability checklist and concomitant medications review will be completed on day 4 postpartum night. During this phone call, the participant will also be asked about any symptoms of COVID-19. If a participant has been screened as positive (answered "yes" to any of the questions), she will be withdrawn from the study.

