## **A Dietary Supplement for Mood Symptoms in Early Postpartum: A Double Blind Randomized Placebo Controlled Trial**

The last dose will be taken in front of the study co-investigator or study RA on day 5 postpartum.

**The second visit** would be the main study day. The timing of each test done during this visit is shown in Table 2. On day 5, the starting time and subsequent time for the procedures may be delayed up to 6 hours in the event of childcare needs or doctor's appointments for the participant; or other similarly important appointments for the participant; or if the study team is unavailable due to multiple births on the same day.

- At the beginning of this visit, participants will have their concomitant medications reviewed and then take the fourth part of the IP. Resting blood pressure and heart rate measurements will be taken. They will do a urine test as well. This test will be considered as a withdrawal criteria. Compliance is also assessed (see more detailed description later in this section). They will also be asked about any neonatal or obstetrical complications.
- Afterwards, they will complete the following instruments:
  - Pittsburgh Sleep Quality Index, contains 9 self-report questions and assesses the sleep quality. This questionnaire will be used to assess the sleep quality of the night before day-5 postpartum.
  - Subjects will go through a neutral mood induction based on the Velten Mood Induction Procedure, which is the most widely used technique for studying affective influences upon behavior and it has demonstrated effectiveness in altering subjective emotional states (Frost & Green, 1982). To facilitate the neutral MIP, participants will also be presented with a piece of neutral music, from work by Clark et al (See full detail below).
  - Following the neutral MIP, subjects will fill out the following questionnaires in the stated order:
    - Visual Analog Scale (VAS) uses a 10-point scale for participants to indicate the extent to which each of the 8 items is consistent with how they feel in the moment; the items included depressed, happy, restless, sad, anxious, angry, drowsy and alert. Within VAS, mood assessment will be done first.
    - Profile of Mood State (POMS) contains of 65 adjectives rated by participants on a 5-point scale. Six factors are derived that include tension, depression, anger, fatigue, vigor and confusion.
    - DAS
    - VAS

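### Protocol 5.1 removes already collected primary-outcome data from randomised women on a late urine result, and nothing keeps withdrawn women in the postpartum-depression calls

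*Protocol*

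**What the plan says.** **Timing of randomisation.** Protocol 5.4.4 places it after the first visit and before birth: "Subjects will be randomized by CAMH pharmacy in a double-blind manner for receiving the dietary supplements". Every withdrawal rule below can therefore act on a woman who already has an allocation.

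**Scope of withdrawal.** The list in 5.1 opens: "Participants who have been enrolled into the study as per the eligibility criteria listed above would be withdrawn from the study". It concerns the study, not only the product. The reasons include severe obstetric or neonatal complications, day-5 urine evidence of substance abuse, and "any allergic reaction or significant side effects to any components of the dietary supplement that would make continued participation harmful". Section 5.4.6 adds a positive answer to the COVID-19 questions on day 3 or on the night of day 4, after which "she will be withdrawn from the study".

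**The urine rule.** Criterion II in 5.1 notes that the result comes 1-2 weeks after the visit and defends the rule by saying that "removal of mood induction data biased by substance abuse would improve data integrity". Section 5.4.6 repeats of the day-5 urine test: "This test will be considered as a withdrawal criteria".

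**What the data are for.** Section 5.5 makes the VAS of depressed mood, before and after the sad mood induction, the primary analysis. Section 4 sets prevention of postpartum depression up to 6 months as the secondary endpoint, and 5.4.7 measures it through four telephone calls.

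**After withdrawal.** Section 5.8 covers only return or disposal of the product. Section 5.9 covers only follow-up of the adverse event.

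**Numbers.** 140 women are to be recruited, and "it is expected 100 subjects to complete the study" (section 1, Methods; likewise 5.1).

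**The concern.** There are two separate problems.

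First, criterion II discards observed primary-outcome data from randomised women because of something learnt after randomisation and after the outcome. The analysed groups are then no longer the groups that were randomised. The decision also has room for discretion. Section 5.4.3 says how a positive screen is read at the first visit, but for day 5 the protocol does not define what amounts to evidence of substance abuse. That judgement is made once the woman's mood response is on file, and section 5.2 itself expects the supplement's effect to be visible in individual women.

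Second, the other rules end study participation when only the product or the home visit needs to end. Read as written, they cost the 6-month depression data in women with complications or intolerance, a group whose later mood bears directly on the secondary objective.

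**Working it through.** **1. The rules side by side**

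| Reason | Timing relative to the day-5 outcome | Fate of the VAS data | Link to arm |
|---|---|---|---|
| Urine evidence of substance abuse (5.1 II, 5.4.6) | Result 1-2 weeks after | Collected, then removed | None evident while blinding holds |
| Side effects that make participation harmful (5.1 III) | Normally before | Normally not collected; no removal stated | Plausible and direct |
| COVID-19 answers (5.4.6) | Day 3 before the first dose, or day 4 night before the third | Not collected | None evident |
| Severe complications (5.1 I, 5.4.5) | First asked before day 3, again on day 5 | Normally not collected; no removal stated | None through the product if known before the first dose |

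Deletion of collected data is written for the first row only.

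**2. Follow-up calls.** A day-5 urine sample with a result after 7 to 14 days reports on about day 5 + 7 = 12 to day 5 + 14 = 19. The Day 10 call may then already have taken place, and the 1-, 3- and 6-month calls are at stake. For women withdrawn before or at day 5, all four calls are at stake. Sections 5.4.7, 5.8 and 5.9 contain no sentence that keeps withdrawn women in the calls, and none that says the calls stop.

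**3. How many could be affected.** Recruited minus completing is 140 - 100 = 40, and 40/140 = 28.6%. The protocol does not say that all 140 are randomised, so this is an upper bound on loss after allocation. No rate is given for any single reason.

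**4. Does power require removing anyone?** The plan's own figure is 80% power for a 25% reduction: 0.25 x 45 = 11.25 mm, SD 12 mm, alpha 0.015 (taken as two-sided, critical value 2.432). Normal approximation: power = Phi(11.25 / (12 x sqrt(2/n)) - 2.432).

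- n = 25 per group (60 less 10 dropouts): 11.25/3.394 = 3.315, power 81.1% (78.2% with the t distribution). This matches the stated 80%.
- n = 30 per group, read literally: 88.5% (86.5% with t). This does not match.
- n = 50 per group (100 completers): 11.25/2.4 = 4.688, power 98.8%.

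Power is ample with everyone kept, so it gives no reason to discard confounded ratings.

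**5. Size of bias, illustrative.** Let a share d of one arm be removed, and let their mean VAS shift be x mm above that of the women retained. The full-arm mean is (retained mean) + d x, so the analysed arm mean is off by d x. If the same happens in both arms the errors cancel. The assumptions, which are not in the documents, are: 70 per arm, removal from the active arm only, no true effect, SD 12 mm, nominal two-sided alpha 0.015.

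| d | x (mm) | Bias d x (mm) | Actual error rate |
|---|---|---|---|
| 2% | 6 | 0.12 | 0.015 |
| 5% | 12 | 0.6 | 0.019 |
| 10% | 12 | 1.2 | 0.033 |
| 10% | 24 | 2.4 | 0.10 |

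Example for the third row: SE = 12 x sqrt(1/70 + 1/63) = 2.08; 1.2/2.08 = 0.58; Phi(0.58 - 2.43) + Phi(-0.58 - 2.43) = 0.033. Against the 11.25 mm effect in 5.6, 0.6 mm is 5% and 2.4 mm is 21%. If removal is unrelated to arm and outcome, the bias is zero.

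**The case against.** The strongest defence is that the only rule ordering deletion rests on a laboratory result obtained under blinding, with no evident link to the arm. Its expected bias is then about zero, and it removes ratings that are hard to interpret. Side-effect withdrawal is limited to cases where continuing would be harmful, and section 2.8 reports no side effects in the open trial, so it may be rare. A statistical analysis plan might also define the analysis sets.

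Much of this stands as to size. It does not rescue the rule. The protocol states the removal and its rationale, so an analysis plan that kept these women would have to contradict it. The undefined criterion, applied after the outcome is known, leaves room for selection if blinding is imperfect.

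Three stronger readings are tempting, and the documents do not support them:

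- **That primary data are deleted for side effects or COVID-19 answers.** No removal is stated for either. The COVID-19 questions precede day 5, so nothing has yet been collected.
- **That 29% of randomised women are lost.** The 140 are described as recruited, and some of the 40 may leave before randomisation.
- **That the urine rule conflicts with the separate opioid criterion.** The urine panel is not described, and two withdrawal criteria can stand together.

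It is also fair to say that the end of the calls is an inference. Some withdrawals, such as after an infant's death, are partly meant to spare the woman burden, so a call will not always be appropriate.

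**Conclusion.** The point holds in this form. Criterion II takes already observed primary-outcome data from randomised women out of the comparison, on a late and undefined finding, so the primary analysis is not as randomised. The other rules lead mainly to outcomes that are not collected. Of these, side-effect withdrawal is the one plausibly related to arm. If withdrawal from the study is followed as written, depression data to 6 months are lost for all these women. That last step is a reasonable inference from the wording and from the absence of any retention clause; the text does not say it outright.

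The size of any bias cannot be known from the documents. Under the assumed one-arm removals it runs from about 0.1 to 2.4 mm, and it is zero if removal is unrelated to arm and outcome. The case for change rests on the principle of analysing as randomised and on the low cost of doing so, and does not depend on a demonstrated large bias.

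**What to change.** Leave the clinical stopping rules as they are and change what follows from them:

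1. Delete the wording in 5.1 criterion II that removes mood-induction data.
2. State that the primary analysis includes every randomised woman with day-5 data, in her assigned arm. Make exclusion of urine-positive women a labelled sensitivity analysis, with the definition of a positive result fixed before unblinding.
3. Separate stopping the product or the home visit from leaving the study. Keep the Day 10, 1-, 3- and 6-month calls for withdrawn women who still consent and for whom contact is appropriate.
4. Report losses after randomisation by arm and reason, separating those before the first dose. Step 2 cannot recover women who leave before the day-5 visit, so this table is needed to judge them.

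The cost is amendment wording, one extra analysis and a few more calls. The downside is that a few women with confounded mood ratings stay in the primary analysis. With about 98.8% power at 50 per group for 11.25 mm, the trial can afford that.
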